### Interventions

#### Provider education

Provider education initiated with introductory webinar lectures from the team’s clinical educators and was delivered to the community providers in rural Utah, with one session in person and then repeated via webinar. This introductory presentation was led by perinatal OUD and pediatric specialists and included an introduction to the topic of OUD among pregnant women, the impact of OUD treatment on maternal health, and an overview of MOUD dosage and practice in relation to NOWS. Ongoing educational sessions are being held monthly using videoconferencing, allowing for case consultation and additional training developed by perinatal OUD and pediatric specialists. For those in the area who cannot attend the monthly webinars, local project partners attended staff meetings or have one-on-one visits to deliver the materials and answer questions. Furthermore, all sessions are recorded and posted on the project YouTube channel (with case consultation discussion not included). Sessions have included topics such as, but not limited to, effective use of urine testing, warm handoffs and referrals, peer support services, and substance use stigma. Furthermore, nursing and medical staff of local clinics and child protective service workers have also been trained in SBIRT using both in person and online modalities.

#### Resource enrichment

In addition to improved provider knowledge and skills through the education portion of this intervention, women who participate in this study receive enriched perinatal care. A nurse care manager hired through the project and embedded in the local women’s health clinic provides care coordination for participants. Nurse care management services involve activities such as regular follow-up with enrolled women between appointments in order to promote ongoing engagement in care; resource identification, referral, and enrollment assistance with relevant resources, such as mental health care, support groups, and social services.

### Analyses

Following study conclusion, we will employ descriptive statistics to calculate measures of central tendency, frequencies, and proportions for patient demographics and substance use, health, social, and mother/child indicators.* T*-tests and* χ*^2^ tests will be used to assess mean and proportional differences in both cross-sectional and changes in repeated measures across study time points for participant outcomes. As this is a pilot study, powered analyses are not the purpose of this project and thus we do not have a target number of participants for enrollment [55]. The research team will not be conducting subgroup or interim analyses.

Qualitative data collected during the community needs assessment will be analyzed using the procedure for Rapid Identification of Themes from Audio Recordings (RITA) described by Neal and colleagues [56]. Though the inclusion of qualitative data can greatly enrich quantitative data, the slow and labor-intensive process of analyzing it can be a barrier due to time constraints [57, 58]. The RITA approach was developed as way to increase the speed of the analysis process while preserving more of the original data. It is applied to the actual audio recordings of semi-structured interviews. The process involves several time-saving steps to improve efficiency of qualitative data analysis. These include pinpointing research foci for which RITA will be used, creating a codebook of key themes identified and their valence (positive, neutral, or negative context), creating a coding form, refining the codebook, coding, and analyzing codes. A key time-saving feature of RITA is that during analysis, audio recordings are broken down into shorter time segments. The coding form is a grid listing themes and time segments, and coders mark the themes present in each time segment [56].

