### Participants

Study participants are comprised of [1] community health-care providers and [2] pregnant women with OUD. Community health-care providers include nurse practitioners, physician’s assistants, obstetricians, pediatricians, family practice physicians, behavioral health care professionals, and child protective services caseworkers practicing within the targeted counties who are willing to participate in the educational sessions delivered by the project team and provide informed consent.

Pregnant women with OUD participants include those who are living in the targeted counties, who are not currently incarcerated, and who provide informed consent. During the intervention phase, women are encouraged to engage in in physical, mental, or behavioral health service by the project nurse care manager that is congruent with the participants needs for prenatal care, OUD recovery, and wellness for mother and fetus. These participants are being recruited with the help of the community-based nurse care manager through posting fliers and communicating directly with potential referral sources, such as local healthcare providers, local health department, and the division of child and family services. The nurse care manager also obtains informed consent. Although the study sample is not powered a priori to achieve a pre-specific treatment effect, a nurse care manager who is well integrated in the local community is part of the research team and leverages relationships with local referral sources to achieve adequate participant enrollment. The nurse care manager obtains locator information for each enrolled participant, and continues checking in with participants to ensure retention and follow-up. The research team meets weekly with the nurse care manager to ensure several follow-up attempts are made for purposes of enrolling and collecting data from participants.

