#### Participant assessments

Women who have provided consent are asked to complete a baseline assessment prior to receiving the intervention. This assessment consists of a series of self-report and interviewer administered questionnaires regarding health, mental health, social service involvement, and substance use. These constructs were selected for assessment given that the interventions and services provided to participants were anticipated to have an impact on these areas. Two follow-up assessments are collected: a pre-delivery follow-up at 34 to 40 weeks of gestation and a post-delivery follow-up 30 days following delivery. These assessments contain the same questionnaires as the baseline assessment, with the exception of the Adverse Childhood Experience scale since these scores are related to childhood experiences and therefore should not vary over the course of the study. We are also collecting data from the woman’s and her infant’s medical records (Table 4). In addition, our team will work with the local department of health to obtain county level data across time at the conclusion of the project to assess intervention impact within the larger community (Table 4). In the event that a participant chooses to discontinue their participation in the study, no additional data will be collected from that participant.

**Table 4 Tab4:** Patient-level study measures

Source	Outcome	Domain	Instrument	Source of data	Baseline	Pre-delivery follow-up	Post-delivery follow-up
Health department	Hepatitis B Virus (HBV)	Health	ICD10 Code B16	Health department	X		X
	Hepatitis C Virus (HCV)	Health	ICD10 Code B18.2	Health department	X		X
	Human Immunodeficiency Virus (HIV)	Health	ICD10 Code B20	Health department	X		X
	Syphilis	Health	ICD10 Code A53.9	Health department	X		X
	Gonorrhea	Health	ICD10 Code A54.9	Health department	X		X
	Chlamydia	Health	ICD10 Code A74.9	Health department	X		X
	Child welfare involvement	Social	ICD10 Code Z62.21	Health department	X		X
	Overdose	Health	ICD10 Cod T40.6	Health department	X		X
Medical record	Pre-eclampsia	Health	ICD10 Code O14	Medical record			X
	Pre-term birth	Health	ICD10 Code O60	Medical record			X
	Cesarean section	Health	ICD10 Code O82;	Medical record			X
	Intrauterine growth restriction	Health	ICD10 Code P05.9	Medical record			X
	Birth weight	Health	ICD10 Code P07	Medical record			X
	Apgar score	Health	ICD10 Code P09	Medical record			X

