	Neonatal opioid withdrawal syndrome (NOWS) severity	Health	ICD10 Code P96.1	Medical record			X
	Length of hospital stay	Health	Discharge dates	Medical record			X
	Continuity of MOUD	QI	Prescriptions Filled	Medical record			X
	Illicit drug use	SUD	Urinalysis	Medical record	X	X	X
	Number of infant ER visits	Health	CPT 99,281–99,285	Medical record			X
	Adequacy of prenatal care	QI	Adequacy of Prenatal Care Utilization (APNCU)	Calculated from medical record			X
Medical record/self-report	Overdose events	SUD	ICD10 Code T40.2X1A	Medical record/Self-report	X		X
Self-report	Overall health	All	12-Item Short Form Survey (SF-12)	Self-report	X	X	X
	Substance misuse	SUD	Adapted Drug Abuse Screening Test (DAST)	Self-report	X	X	X
	Trauma history	Social	Adverse Childhood Experience (ACE)	Self-report	X		
	Alcohol misuse	SUD	Alcohol Use Disorders Identification-Concise (AUDIT-C)	Self-report	X	X	X
	OUD	SUD	Diagnostic and Statistical Manual 5 (DSM-5) Opioid Use Disorder (OUD) Checklist	Self-report	X	X	X
	Depression	Mental Health	Edinburgh Postnatal Depression Scale (EPDS), Patient Health Questionnaire-9 (PHQ-9)	Self-report	X	X	X
	Nicotine dependence	SUD	Fagerstrom Test for Nicotine Dependence (FTND)	Self-report	X	X	X
	Anxiety	Mental health	Generalized Anxiety Disorder-7 (GAD-7)	Self-report	X	X	X
	Psychological distress	Mental health	Kessler Psychological Distress Scale (K6)	Self-report	X	X	X
	Parental knowledge & skills	Social	Parenting and Family Adjustment Scale (PAFAS)	Self-report	X		X
	Patient satisfaction	QI	Patient Satisfaction Questionnaire Short Form (PSQ-18)	Self-report		X	X
	Patient utilization of services	QI	Treatment Services Review-6 (TSR-6)	Self-report	X	X	X
	Post-traumatic stress disorder (PTSD)	Mental health	Primary Care PTSD Screen for DSM-5 (PC-PTSD-5)	Self-report	X	X	X

*QI* quality improvement, *SUD* Substance Use Disorder, *IC10* International Classification of Disease, 10th Revision, *CPT* Current Procedural Terminology

Our team chose several reliable and valid self-report instruments to assess substance use at the patient-level. The Alcohol Use Disorders Identification-Concise (AUDIT-C) is a measure of unhealthy alcohol use [40]. The Diagnostic and Statistical Manual 5 (DSM-5) OUD Checklist is an instrument to assess OUD [41]. The Fagerstrom Test for Nicotine Dependence (FTND) captures the presence of nicotine dependence [42]. Finally, we adapted the Drug Abuse Screening Test (DAST) [43] to assess opioid-specific participant behaviors.

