## Limitations

While this study has several strengths including its focus on implementation of evidence-based care, targeting an underserved population within rural communities, and the inclusion of providers, its limitations should be discussed. This implementation intervention was designed for a specific rural community, which could potentially limit generalizability of the findings; however, rural counties across the US appear to be experiencing similar challenges, [5] and this intervention may be adapted for site-specific needs. This study is a single arm trial with no control group, and therefore evaluation through an implementation framework, like RE-AIM, is critical in adequately assessing the study’s effect on intervention effectiveness, uptake and sustainability.

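### OUD is both the entry condition and a tested before-after outcome, so a test of OUD status is largely one-directional and biased toward improvement

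*Protocol article*

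**What the plan says.** The Participants section defines the patient sample by the disorder: "Study participants are comprised of [1] community health-care providers and [2] pregnant women with OUD". The listed conditions concern residence, incarceration and consent: "Pregnant women with OUD participants include those who are living in the targeted counties, who are not currently incarcerated, and who provide informed consent". No instrument, cut-off or currency requirement is given for establishing OUD at entry.

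Table 4 (Participant assessments) has OUD in its Outcome column, measured by the "Diagnostic and Statistical Manual 5 (DSM-5) Opioid Use Disorder (OUD) Checklist", self-reported, and marked at baseline, pre-delivery and post-delivery. The text below the table says that the "OUD Checklist is an instrument to assess OUD". On the follow-ups the same section says: "These assessments contain the same questionnaires as the baseline assessment, with the exception of the Adverse Childhood Experience scale".

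The Analyses section states the scope of testing: t and chi-square "tests will be used to assess mean and proportional differences in both cross-sectional and changes in repeated measures across study time points", for participant outcomes, with no item of Table 4 exempted. It also says "we do not have a target number of participants for enrollment". The Limitations section acknowledges that "This study is a single arm trial with no control group". It does not mention that an entry condition is also tested for change.

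**The concern.** A before-after test asks whether follow-up differs from baseline. That question is informative about a programme only if, without the programme, movement in either direction were about equally likely. Selecting women because they have OUD breaks this for OUD status. If nearly all are positive at the start, nearly all movement must be from positive to negative. Women who would have stopped meeting criteria anyway, or who under-report near delivery, count as improvement, and few or none are left to move the other way.

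This differs from the general weakness of a single-arm design, because it comes from testing the selection variable itself and can be removed by not testing it. Pairing the analysis does not remove it.

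At stake is how a significant fall would be read. The Efficacy part of Table 2 asks how effective the services were in improving care, using patient and record data. A small p-value for OUD could be taken there as evidence of benefit when a fall was expected regardless.

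**Working it through.** The article states no sample size, alpha or expected change, so there is no figure of its own to reproduce. What follows is an illustration.

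**Inputs**
- From the article: OUD defines the patient sample; OUD is measured by the checklist at all three time points; t and chi-square tests are applied to change; there is no control arm.
- Assumed: two-sided alpha 0.05; N = 20, 30 or 40 women; baseline 100% positive; a share d = 5%, 10% or 20% no longer meeting criteria at follow-up with no programme effect.

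**Yes/no scoring: how many reversals give p < 0.05**

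Let k be the number of women positive at baseline and negative at follow-up. None can go the other way.

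- Uncorrected chi-square comparing N/N with (N − k)/N positive: χ² = 2Nk/(2N − k). For N = 20: k = 3 gives 120/37 = 3.24, not significant; k = 4 gives 160/36 = 4.44, significant (critical value 3.84). For N = 40: k = 3 gives 240/77 = 3.12 and k = 4 gives 320/76 = 4.21. Four reversals suffice at all three sizes.
- Exact McNemar with all discordances one way: p = 2 × 0.5^k. k = 5 gives 0.0625 and k = 6 gives 0.031. Six reversals are needed.

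**Chance of a significant fall with no programme effect**

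This is P(K ≥ 4) or P(K ≥ 6), with K binomial(N, d):

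| d | Test | N = 20 | N = 30 | N = 40 |
|---|---|---|---|---|
| 5% | chi-square | 2% | 6% | 14% |
| 5% | exact McNemar | <1% | <1% | 1% |
| 10% | chi-square | 13% | 35% | 58% |
| 10% | exact McNemar | 1% | 7% | 21% |
| 20% | chi-square | 59% | 88% | 97% |
| 20% | exact McNemar | 20% | 57% | 84% |

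Worked entry: N = 20, d = 10%. P(K = 0, 1, 2, 3) = 0.122, 0.270, 0.285, 0.190, which sum to 0.867, so P(K ≥ 4) = 0.133. The chance of a significant worsening is zero in every cell. A valid two-sided 5% test would give about 2.5% in each direction.

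**If something other than the checklist decides entry**

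Suppose entry rests on a referral or an existing diagnosis. Baseline and follow-up checklists are then both later measurements. With unchanged true status and independent error, the expected proportion positive is the same at both visits, so retest error alone adds no directional bias. Natural remission and greater under-reporting at follow-up still push the proportion down.

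**Criterion count analysed by t-test**

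Scores can then move both ways. A simulation assumed a 0 to 11 count, entry at 2 or more criteria, SD 2, reliability 0.6 to 0.9 and no true change:
- Population mean 4: spurious mean fall of 0.05 to 0.17 criteria; false improvement 4.1% to 6.0% at n = 20 and 5.2% to 9.5% at n = 50, against a nominal 2.5%.
- Population mean 6: spurious fall of about 0.02 criteria or less; false improvement about 3%.

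The bias therefore depends on how close enrolled women are to the cut-off.

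**The case against.** The strongest objection is that the article does not say the checklist decides entry. Women are recruited through fliers and referral sources, and the baseline assessment follows consent. Baseline may then be below 100%, some women could move from negative to positive, and retest error need not favour the programme. This stands, and it limits the size of the bias. It does not remove natural course and under-reporting in women chosen for having the disorder.

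Second, the aims are modest. The patient-level aim in the Design section is abstinence and treatment engagement, OUD status is one of more than 30 rows in Table 4, the effect is called preliminary, the study is called a pilot, and the missing control group is disclosed. This keeps the point from being a major one. The disclosure, however, does not cover testing the entry condition for change.

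Third, a separate analysis plan might fix the scoring or exempt this item. That is possible, but the article itself states the scope of testing and exempts nothing.

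A reader might infer more than the article supports:
- *That the no-change null cannot be reached.* With yes/no scoring it is a boundary value, attained if every woman remains positive. With low reversion and small N the error rate falls below 5%. With a count it is plainly reachable.
- *That a severity score would show false improvement in most studies.* Rates of 50% to 86% arise only if entry is confined to the top 20% of the score distribution, with selection on the baseline score itself. Nothing in the article supports that.

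**Conclusion.** The point holds in a conditional form. OUD defines the patient sample, is listed as an outcome at every time point, and falls within the tests of change in a study with no control arm. A before-after test of OUD status is therefore largely one-directional and tilted toward improvement.

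With baseline at 100%, 10% to 20% reverting and N = 20 to 40, the chance of a significant fall without any effect is about 13% to 97% by uncorrected chi-square and 1% to 84% by exact McNemar. At 5% reverting it ranges from under 1% to 14%. N, the reversion share and full positivity at baseline are all assumptions. If entry rests on something other than the checklist, retest error may contribute nothing, and natural course and under-reporting remain. For a criterion count the bias is modest to negligible under the assumed entry cut-off of 2 or more criteria.

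The article does not establish that the null is unreachable or that false improvement is near certain. It does support the conclusion that a p-value for the fall in OUD status from baseline cannot be read as evidence of effect.

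**What to change.** In Analyses, add a sentence or two:
- Exclude OUD status by the DSM-5 checklist from the baseline-to-follow-up significance tests.
- Report the proportion still meeting OUD at each follow-up with an exact 95% confidence interval.
- State that, because OUD is the entry condition, a fall from baseline is not by itself evidence of effect.
- If a criterion count is used, report its change descriptively with a confidence interval and the same caveat.

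Testing pre-delivery against post-delivery instead is not a good substitute, because it discards the only measurement taken before the intervention.

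The cost is one p-value that would tend to look favourable but could not be interpreted. No data collection changes.

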### Data management

All data is stored on password-protected computers or in locked cabinets. Participant identifiers are stored separately from the coded participant data, audio recordings will be destroyed at the end of the study. Study data and documentation monitoring occurs monthly throughout the study and is conducted by the principal investigator and nurse care manager. Study findings will be reported via peer-reviewed publication, a final report to the state of Utah, and national presentations.

### Harms

Potential harms to participants are minimal. For providers, minor psychological risks may include feelings of inadequacy if they are not currently following or have insufficient knowledge of current opioid use treatments for pregnant women. Participants who have treated or are currently treating pregnant women with opioid use disorder may experience feelings of guilt if personal biases or stigmas are uncovered towards pregnant women using opioids. There may be a risk of loss of confidentiality. The project leadership team will meet weekly with the nurse care manager to ensure adherence to the protocol when enrolling and treating patient-level participants.

For patients, the baseline and follow up appointments, patients are asked questions about private, personal matters. The assessments ask demographics, medication adherence, substance use and co-morbid conditions such as pain, depression, etc. The risk of harm is the same as regular health care treatment. Some answers given in research visits (like whether patients use illegal drugs or have ever been arrested) might put them at risk if ever there is a breach of privacy; however, we do not anticipate such a breach. There are no known psychological risks associated with the interview questionnaires or procedures in this study. It is possible that discussion of sensitive topics such as substance use may cause emotional discomfort in some participants. There may also be risks of, emotional distress, inconvenience and possible loss of privacy and confidentiality associated with taking part in a research study.

Medical and psychological support is available through local partnering agencies. If medical needs arise that cannot be addressed at a partnering clinic, the patient will be transported to the local hospital. The research team does not anticipate needing to stop the provider or patient interventions. Providers will be encouraged to offer evidence-based treatment practices for all participants, and treatments provided to participants will be tailored to support the patient’s preferences and individual needs. This project does not have an official Data Monitoring and Safety Board; however, the Principal Investigator and research staff will routinely monitor all aspects of the study conduct and documents, and implement corrective actions as any deviations are observed.

## Discussion

This study protocol is of a type 1 hybrid effectiveness-implementation intervention [28] using two implementation frameworks to guide and assess the success of a perinatal OUD education intervention in a rural community. The hybrid type 1 design allows the research team to focus on clinical effectiveness monitoring while also gathering information on the implementation of the intervention [28]. Given the urgent need for identifying methods for implementing evidence-based practices to treat OUD among pregnant women, we chose to use this hybrid effectiveness-implementation design to help disseminate state-of-the-art-treatment as quickly and efficiently as possible [28]. Our hybrid type 1 is specifically examining the intervention at the patient level, while observing the implementation process and barriers.

Combining two implementation frameworks to supplement one another is commonly used in the literature [59–62]. The CFIR is comprehensive regarding the assessment, and the RE-AIM framework is the intervention approach. The CFIR was employed at the beginning of the study to assess for contextual factors that may affect implementation and throughout the project to assess impact. The CFIR is a large implementation framework, and has been employed extensively to assess MOUD interventions [63]. Previous research shows that tailoring the CFIR to focus more on patient needs within the *outer setting* domain improves its utility in outpatient healthcare settings [64]. With this in mind, it may be useful for our research team to focus in more specifically on this domain during implementation of our intervention. The CFIR was also used in a narrative review of 20 published articles to evaluate attitudes towards prescribing BUP [63]. This review found that the domains *intervention characteristics, outer setting,* and *inner setting* were represented in the analysis, and concerns about diversion, self-efficacy in prescribing, philosophical objections, and stigma were identified as top barriers to BUP prescribing. Our project aims to improve provider self-efficacy in caring for pregnant women with OUD and reduce stigma, addressing the barriers identified in the aforementioned study. Knowledge derived from our project regarding barriers to adoption of the intervention have been and will continue to be used to guide the topics of our webinars and other forms of provider education.

Due to the physical distance between the community of interest and the research team, the use of video and telecommunication is key in delivering this intervention. Previous research has adapted the CFIR to assess readiness for and suitability of a tele-mentoring platform, the Project Extension for Community Healthcare Outcomes (ECHO), and created ECHO-specific organizational readiness questions and a process guide for implementation [65]. Using the CFIR as a guide for our project may also yield information that can be adapted and utilized as guidelines for other interventions involving OUD-specific remote education.

The RE-AIM framework was chosen to evaluate the implementation of this provider education intervention because RE-AIM is an established tool for comprehensively assessing multilevel interventions and contains a dimension for assessing efficacy of the intervention itself (Table 2) [27]. The RE-AIM evaluation framework may also be useful in implementing an intervention similar to ours on a larger scale. This framework was utilized by McNeely and colleagues to rigorously evaluate an OUD treatment consult model in a large multi-site trial, generating knowledge for how OUD treatment practices can be widely disseminated and adopted across healthcare systems [59]. Similarly, we may be able to apply our RE-AIM evaluation findings to larger scale interventions.

This study is being conducted in the midst of an ongoing opioid crisis in the US, [66] which is increasingly affecting pregnant women and women of child-bearing age [67]. Rural pregnant women and their infants have been severely affected as a group, [68] yet there is a gap in research around evidence-based treatment for perinatal OUD. By measuring treatment outcomes of MOUD specifically among pregnant women, this study is contributing to an emerging knowledge base, which can be utilized to help address the issue of OUD within this high-need population. Specifically, our intervention may benefit this population by providing wrap-around services through the support of a care manager, and enhancing quality of prenatal care by training community providers in best evidence-based practices for perinatal OUD and NOWS treatment. The findings derived from this study will benefit the field at large by providing evidence for models of care for pregnant women struggling with OUD, and informing implementation of similar interventions across the country.

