To what extent did perinatal addiction education reach the pregnant women with OUD within the healthcare system in Your Counties?	Local healthcare and social service agencies	Electronic medical records; health department records	Number of patient participants/ total number of pregnant women with opioid misuse in Your Counties during the study duration
Efficacy			
How effective was the provider training and support?	Community providers	Questionnaires assessing skills, knowledge and satisfaction	Mixed method surveys regarding provider experience and skillset
How effective were perinatal addiction education services in improving care for pregnant women with OUD?	Healthcare and social service records; patient participants	Compare data regarding illicit substance use, MOUD continuity, opioid poisoning occurrences, physical and mental health, and social service involvement; questionnaires to assess patient perception	Medical codes; standardized comprehensive wellness measurement instruments; qualitative surveys
Adoption			
To what extent are community providers using perinatal addiction education practices when treating patients with perinatal OUD?	Community providers; local healthcare agencies	Questionnaires assessing provider practices and attitudes; electronic medical records	Mixed methods surveys regarding provider practices; frequency of MOUD provision, NOWS treatment and SBIRT by participating community providers
To what extent are patients utilizing resources made available through the perinatal addiction education program?	Partnering agencies (e.g. EUWH, Four Corners Behavioral Health); medical records; pharmacy records	Interviews with partner agencies; electronic medical record and pharmacy record evaluation	Utilization of care management and resources made available through this project; number of MOUD prescriptions filled; presence of BUP in urinalysis via medical record
Implementation			
What were the barriers and facilitators of high quality care?	Community providers	Questionnaires and focus groups	Perceptions of and feedback regarding the implementation kickoff event, as well as ongoing training and support provided via the implementation of perinatal addiction education
Maintenance			

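### The MOUD continuity outcome has no scheduled baseline or named comparator, and the Discussion's claim to measure MOUD treatment outcomes has no supporting analysis

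*Protocol article*

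**What the plan says.** - **Schedule (Participant assessments, Table 4).** The row reads "Continuity of MOUD QI Prescriptions Filled Medical record X", and its single mark stands in the post-delivery column. That visit is "a post-delivery follow-up 30 days following delivery".
- **Use of the outcome (Implementation framework, Table 2, Efficacy).** The method is: "Compare data regarding illicit substance use, MOUD continuity, opioid poisoning occurrences, physical and mental health, and social service involvement". No comparator is named.
- **Other MOUD data (Table 2, Adoption).** The measures include "number of MOUD prescriptions filled; presence of BUP in urinalysis via medical record", with medical and pharmacy records as sources.
- **Analyses.** t-tests and chi-square tests are planned, both cross-sectionally and for change across time points. The section adds: "The research team will not be conducting subgroup or interim analyses".
- **Design and Limitations.** There is one group and no control. The patient-level objective concerns what provider education does for abstinence from illicit opioids and for engagement in treatment.
- **Participants.** Entry requires pregnancy with opioid use disorder, residence in the two counties, not being incarcerated, and consent. Being on MOUD is not a condition, and no gestational-age limit is given.
- **Discussion.** The study is said to contribute "By measuring treatment outcomes of MOUD specifically among pregnant women, this study is contributing to an emerging knowledge base".

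**The concern.** There are two linked problems.

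First, treatment engagement is one of the two patient-level targets, and filled MOUD prescriptions are a direct record of it. With no control arm, the natural comparator for a post-delivery value is the same woman's earlier value. The plan schedules none for this outcome. A post-delivery figure alone does not separate women who were already on MOUD at enrolment from women who started it during the programme.

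Second, a reader of the Discussion would expect the study to report how women do on MOUD. Nothing in the objective, eligibility or analyses is set up to produce that. If the sentence carries through to the results paper, before-after changes in a mixed cohort could be read as outcomes of the medication.

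**Working it through.** The plan states no sample size, rate or effect size for this outcome, so there is no figure to reproduce. The check sets the sections side by side.

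**Step 1. Do the items compared in Table 2 have a baseline in Table 4?**

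| Item in Table 2 (Efficacy) | Matching row in Table 4 | Time points marked |
|---|---|---|
| Illicit substance use | Urinalysis | 3 of 3 |
| MOUD continuity | Prescriptions filled | 1 of 3 (post-delivery) |
| Opioid poisoning | Overdose events | 2 of 3 (baseline, post-delivery) |
| Physical and mental health | SF-12, PHQ-9 and others | 3 of 3 |
| Social service involvement | Child welfare code | 2 of 3 (baseline, post-delivery) |

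MOUD continuity is the only one of the five without any row that carries a baseline mark.

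**Step 2. Does a mark show the period described or the date of extraction?** The text under Participant assessments says the county data are obtained when the project ends. Yet all eight health-department rows are marked at baseline and post-delivery. Urinalysis comes from the medical record and is marked at all three time points. For these rows the columns show the period a value describes. Read the same way, the MOUD row has no baseline. The reading is not certain: adequacy of prenatal care is marked post-delivery only, although it looks back over the pregnancy.

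**Step 3. Do other sources fill the gap?**
- Buprenorphine in urinalysis (Table 2, Adoption): urinalysis is scheduled at all three time points, but the Table 4 row is for illicit drug use. Presence on one day is not continuity, and methadone, which the Background also names as a treatment, is not covered.
- Medication adherence (Harms): asked at baseline and follow-up, but not tied to MOUD and without a row in Table 4.
- TSR-6: scheduled at all three time points, but the article does not say that it captures MOUD.

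Each is partial.

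**Step 4. Is the reference period for fills defined?** No period is stated. Because entry has no gestational-age limit, the time from enrolment to the post-delivery visit will differ between women. A raw count of fills since enrolment would then partly reflect how early a woman joined.

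**Step 5. What a baseline adds (assumed figures).** Change = share on MOUD post-delivery minus share on MOUD at entry. With 50% post-delivery:
- entry 30%: 50 - 30 = +20 points
- entry 50%: 50 - 50 = 0 points
- entry 70%: 50 - 70 = -20 points

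This treats the outcome as status at one time, which the plan does not specify. It shows only that a post-delivery share by itself fits a rise, no change or a fall.

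**Step 6. Does any analysis support the Discussion sentence?** MOUD is not the intervention, which is provider education plus nurse care management. It is not an entry condition. It is not named as a factor in Analyses, and subgroup analyses are excluded. None of the described analyses yields outcomes of MOUD.

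**The case against.** The strongest reply is that the single mark may be only the point of abstraction. Fill records are dated and retrospective, and continuity is by nature a measure over time, so one reading after delivery can cover the whole pregnancy. Table 2 does not say what the comparison is with, and Analyses allows cross-sectional as well as repeated-measures tests. A condensed article may leave the reference period to a fuller document. The Discussion sentence is background prose; the stated aim concerns provider education, and the article acknowledges both its pilot status and the absence of a control.

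Much of this stands, and it limits the point. A reader might infer that MOUD is recorded only after delivery, that the Table 2 comparison cannot be made, or that a fall in MOUD use would go unseen. The documents do not support these readings. Urinalysis and the adherence questions give some earlier information, dated fills could supply a baseline, and a gap in fills is just what a continuity measure could show. Nor does the article say that women already on MOUD will be counted as programme successes.

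Two things remain. The article does not merely leave the timing open: it gives a schedule, and that schedule provides no baseline for an outcome it says will be compared. And the Discussion makes a positive claim that the article's own objective, eligibility and analyses do not bear out. An unseen fuller document could settle the first point, but would not make the published sentence consistent with the published design.

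**Conclusion.** The point holds in two parts.

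1. The named MOUD outcome is scheduled at 1 of 3 time points, so the promised comparison and the tests of change have no scheduled baseline and no named comparator. This rests on reading the Table 4 columns as the period described, which the health-department and urinalysis rows support. If the mark means abstraction date, the remaining defect is the unstated reference period and comparator.
2. The statement that the study measures treatment outcomes of MOUD is not supported by the design or analyses described. This does not depend on how Table 4 is read.

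The size of any misreading cannot be calculated from the documents; the +20, 0 and -20 point figures rest on assumed entry shares. This is an inexpensive improvement that should be made. It does not affect the other patient-level outcomes that carry baseline marks.

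**What to change.** - **Table 4:** mark "Continuity of MOUD" at baseline and pre-delivery as well as post-delivery.
- **Definition:** from the medical and pharmacy records already listed, derive each woman's MOUD status at enrolment. Count fills over a stated reference period of comparable length at each time point; 30 days is one possible choice.
- **Table 2 and Analyses:** name the baseline value as the comparator and report within-woman change. State how buprenorphine in urinalysis and the adherence questions will be used, if at all.
- **Discussion:** say that the study describes outcomes of women receiving the education and care-management programme, give the share who received MOUD, and state that it does not estimate outcomes of MOUD.

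The cost is a longer look-back in an abstraction already planned, edits to two tables and the Analyses text, and one reworded sentence. No new visits are needed. Abstracting the baseline value at enrolment would also secure it for women who later leave, since no further data are collected after discontinuation.
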